# Comparison of the open kinetic chain and closed kinetic chain strengthening exercises on pain perception and lower limb biomechanics of patients with mild knee osteoarthritis: a randomized controlled trial protocol

**DOI:** 10.1186/s13063-022-06153-8

**Published:** 2022-04-15

**Keywords:** Home-based exercise program, Knee osteoarthritis, Physiotherapy

## Abstract

**Background:**

Clinical recommendations suggest exercises as the main treatment modality for patients with knee osteoarthritis (OA). This study aimed to compare the effects of two different exercise interventions, i.e., open kinetic chain (OKC) and closed kinetic chain (CKC) exercises, on the pain and lower limb biomechanics of patients with mild knee OA.

**Method:**

A total of 66 individuals with painful early knee OA, aged 50 years and above, with body mass index (BMI) between 18.9kg/m^2^ and 29.9 kg/m^2^ in Kelantan, Malaysia, will be recruited in this study. Participants will be randomly allocated into three different groups, either the OKC, CKC, or control groups. All three groups will attend an individual session with a physiotherapist. The participants in the OKC and CKC groups will perform the exercises three times weekly for 8 weeks at their home. The control group will receive education about clinical manifestations, risk factors, diagnosis, treatment, and nursing care for knee via printed materials. The primary outcomes include self-reported pain scores (visual analog scale), disability scores (Western Ontario and McMaster Universities Arthritis Index), and quality of life scores (Osteoarthritis Knee and Hip Quality of Life). Secondary outcomes include lower limb biomechanics during gait and sit-to-stand as well as isokinetic knee strength. The outcomes will be measured before and after the intervention.

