To date, open kinetic chain (OKC) and closed kinetic chain (CKC) exercises have been prescribed for knee OA patients. During OKC exercise, the distal segment of the body parts is not fixed, and it can move freely. Knee extension in the sitting position and straight leg raising (SLR) in the lying position are examples of OKC exercises. On the other hand, during CKC exercise, the distal segment of body parts remains stationary on the ground. Examples of CKC exercises include squat and leg press exercises. Both types of exercises were comparable in terms of their impact on improving pain scale, functional scores, and strength [16]. Moreover, 12 weeks of OKC, CKC, and its combination were found to significantly increase the static and dynamic quadriceps strength and thigh muscle bulk in a study that involved 96 patients with knee OA [17]. However, there is a lack of published studies that evaluate the impact of OKC and CKC on the lower limb biomechanics during gait and STS.

Exercise intervention for OA is usually conducted in the hospital or clinic under the supervision of physiotherapists. However, some patients might face logistics constraints in attending the exercise sessions [18]. To improve the adherence to exercise program, the sessions can be relocated from the hospital to other settings such as at home and in the community [7]. Apart from that, patient education is vital to improve the patients’ understanding of their current condition and to ensure compliance to exercise program and long-term self-management at home [12].

The primary aim of this randomized controlled trial (RCT) is to compare the effects of home-based OKC and CKC exercise intervention programs on pain (visual analog scale), disability scores (Western Ontario and McMaster Universities Arthritis Index), and quality of life scores (Osteoarthritis Knee and Hip Quality of Life) among patients with mild knee OA. Our secondary aim is to compare the effects of OKC and CKC exercises on lower limb biomechanics during walking gait and STS tasks. It is hypothesized that OKC and CKC exercises will result in a significant reduction of pain as well as improved functions and quality of life after 8 weeks of intervention. We also hypothesize a small but clinically relevant change in their biomechanical variables following OKC and CKC intervention. These changes may be significant when compared to the usual care group.

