### Sample size calculation

The sample size was determined using G*Power statistical software version 3.1.9.2 (Universität Düsseldorf, Germany) based on the primary outcome variables of pain and function based on the visual analog scale (VAS) scores as well as the Western Ontario and McMaster Universities Arthritis (WOMAC) Index respectively. The sample size for this study was determined to detect an effect size of 0.5, based on a previous study [21] with an alpha value of 0.05. Eighteen participants per group will be sufficient to achieve a statistical power of 0.8. By anticipating a dropout rate of 20%, a total of 22 participants per group (total *N* = 66) will be recruited.

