#### Functional disability

The Western Ontario and McMaster Universities Arthritis Index (WOMAC) Likert version 3.1 will be used to assess functional disability [31, 34]. The WOMAC includes 24 questions. Each question will be scored using five response options ranging from 0: none, 1: mild, 2: moderate, 3: severe, to 4: extreme [31, 34]. WOMAC is designed to assess the patients’ pain perception, stiffness, and disability. The scores will be summed within the three domains, giving a total score for pain (range: 0–20), stiffness (range: 0–8), and disability (range: 0–68) [31]. Higher scores indicate greater severity across the three domains [31, 34]. The Malay version of the WOMAC (M-WOMAC) will be used in this study to better cater to the local cultural background and language spoken in the Malaysian population [35]. Based on a survey that was conducted to test the reliability and validity of the M-WOMAC among 61 women aged 45–65 years in Malaysia, the Cronbach’s alpha of 0.976 showed that the M-WOMAC was valid and reliable to be used among the local population with knee OA [35].

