### Statistical analysis

Data will be entered and analyzed using SPSS version 25 (IBM Corp., Armonk, NY, USA). Only the data from the participants who have completed at least 75% of the study intervention will be analyzed. Data from drop outs will not be included in the analysis. Descriptive data will be reported as a mean ± standard deviation. Two-way ANOVA will be used to test the within- and across- group comparison of the VAS, WOMAC, and OAKHQOL scores, and isokinetic knee muscle strength, as well as lower limb biomechanics during gait and STS. The level of significance is set at a *p*-value < 0.05. A least significant difference (LSD) post hoc test will be conducted following any significant differences from the two-way ANOVA test.

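### Three unranked primary outcomes are each tested at 0.05 with no familywise control, and the trigger for the LSD group comparisons is too loosely worded

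*Protocol article*

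**What the plan says.** All references are to the protocol article.

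- **Abstract, Method:** "The primary outcomes include self-reported pain scores (visual analog scale), disability scores (Western Ontario and McMaster Universities Arthritis Index), and quality of life scores". None of the three is put first.
- **Background:** "The primary aim of this randomized controlled trial (RCT) is to compare the effects of home-based OKC and CKC exercise intervention programs on pain", and the sentence goes on to WOMAC disability and OAKHQOL quality of life. The three stand side by side again.
- **Statistical analysis:** each outcome goes through a two-way ANOVA covering within-group and across-group comparisons. "The level of significance is set at a *p*-value < 0.05". Then: "A least significant difference (LSD) post hoc test will be conducted following any significant differences from the two-way ANOVA test".
- **Sample size calculation:** the number is "based on the primary outcome variables of pain and function", measured by VAS and WOMAC, and "based on a previous study [21] with an alpha value of 0.05". Quality of life does not enter, and alpha is not split.
- **Functional disability:** "The scores will be summed within the three domains" (pain, stiffness and disability). The Statistical analysis section says only WOMAC, without naming a domain.

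No multiplicity adjustment, testing order or success rule appears anywhere in the article.

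**The concern.** A level of 0.05 describes the error rate of one test. With three primary outcomes, each able to support a claim, it no longer describes the error rate of the trial's primary conclusion. This is not detail left to an analysis plan: the article itself fixes the level, the test, the post hoc method and its trigger.

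The second issue is LSD, which makes no adjustment of its own. With three groups it is protected only when it follows a significant test of the group contrast. A two-way ANOVA of group and time also produces a time effect. All three arms receive usual care, including painkillers and education, and entry requires a VAS of at least 2. Improvement in every arm is therefore plausible even if the exercises add nothing. If such a time effect could open the three pairwise group tests, they would run without protection.

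At stake is whether a reported benefit of OKC or CKC on a primary outcome carries the 5% error rate that readers will assume. The trial plans for only 18 evaluable participants per group.

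**Working it through.** **The plan's own figure.** The only error rate stated is 0.05 per test. No familywise figure is given, so there is none to reproduce beyond confirming that one test holds its level: a simulated single group-by-time test gave about 5.0%.

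**Inputs from the article**
- Primary outcomes: 3 (Abstract; Background).
- Level: 0.05 each (Statistical analysis).
- Groups: 3, hence 3 pairs per outcome (Abstract).
- Evaluable participants: 18 per group, 54 in all (Sample size calculation).
- Measurement before and after the intervention (Abstract). With two time points, the group-by-time test equals a one-way ANOVA of change, with 2 and 51 degrees of freedom.

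**Assumptions, not in the article**
- Correlation between outcomes: 0 to 0.9.
- Pre-post correlation: 0.5.
- Improvement common to all arms: 0.5 SD for the LSD step.

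**Step 1. Three outcomes, one group-by-time test each, no true group difference**

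Independent outcomes: 1 − (1 − 0.05)³ = 1 − 0.857 = 0.143.

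Correlated outcomes (simulation, 18 per group):

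| Correlation between outcomes | At least one false claim |
|---|---|
| 0 | about 14% |
| 0.5 | about 13% |
| 0.7 | about 11% |
| 0.9 | about 9% |

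The rate exceeds 5% at every correlation tried.

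**Step 2. LSD within one outcome, no true group difference**

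- The time test with a 0.5 SD common improvement and pre-post correlation 0.5: the SD of change is √(2 × (1 − 0.5)) = 1 SD, so the noncentrality is 54 × 0.5² = 13.5 on 1 and 51 degrees of freedom. Power is 95%, so the time effect is nearly always significant.
- LSD run only after a significant group-by-time test: about 5% per outcome. LSD adds no error here.
- LSD run after a significant time or group-by-time effect: about 12% per outcome.

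**Step 3. Effect of the correction**

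- The first Holm step tests the smallest p-value at 0.05/3 = 0.0167. With independent outcomes and no true difference, the familywise error is 1 − (1 − 0.0167)³ = 4.9%.
- Power cost: the article does not say which effect-size metric its 0.5 is. Reading it as Cohen's f, a one-way F test with 54 evaluable has power 90.2% at 0.05, 83.9% at 0.025 and 79.6% at 0.0167.

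**The case against.** **No any-one-wins rule is stated.** This is true, and the Background hypothesis joins reduced pain with improved function and quality of life. If all three had to succeed, no alpha split would be needed. But that sentence is a hypothesis, not a decision rule, and the sample size covers only two of the three outcomes. The inflation is therefore conditional on any single success counting, which the article leaves open.

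**LSD is normally used to follow up the effect that was significant.** On that ordinary reading a time effect leads to comparisons over time, not between groups, and LSD with three groups holds 5% per outcome. This objection largely stands. The article does not say that a time effect opens the group comparisons; its wording merely fails to exclude it. The 12% is a consequence of one literal reading.

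**A reader might count five primary scores, because WOMAC yields three totals.** Five independent tests would give 1 − 0.95⁵ = 22.6%. The article does not support that count. The Abstract and Background call the WOMAC outcome disability, the measure's own section is headed Functional disability, the sample size pairs WOMAC with function, and the Discussion gives its relevance threshold for the function subscale. The sentence on three domains describes how the instrument is scored.

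**A reader might infer that the article contradicts itself on what is primary.** Basing the sample size on pain and function does not say that only those two are primary.

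**A reader might suspect a hidden Bonferroni split,** since 18 per group gives 79.6% power at 0.0167 if f = 0.5. The section states an alpha of 0.05, so that cannot be assumed.

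**Conclusion.** The concern holds in a limited form. Three unranked primary outcomes, each at 0.05, give a familywise error of about 14% if independent and about 9% to 13% at correlations of 0.9 to 0.5, provided success on any one is enough for a primary claim. The correlations are assumed.

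The LSD sentence is a separate, smaller defect of wording. It is harmless if gated on the group-by-time test (5% per outcome). It is about 12% per outcome only if a common time effect may open the group comparisons, under the assumed 0.5 SD improvement and pre-post correlation of 0.5.

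One could combine the two into 1 − 0.88³ = 32%. That figure stacks the literal LSD reading, an assumed common improvement and independence of three self-reports from the same patients. Under the same literal reading it falls to about 28% at correlation 0.5 and 19% at 0.9. It should not be presented as the trial's error rate.

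**What to change.** 1. State that the WOMAC primary score is the disability (function) subscale, and name one OAKHQOL score as primary. The Quality of life section describes domain items, separate items and an overall score, so the choice needs stating.
2. Control the familywise error across the three primary group-by-time tests. Either use Holm (smallest p at 0.0167, next at 0.025, last at 0.05), or a fixed order such as VAS, then WOMAC disability, then OAKHQOL, each at 0.05 and stopping at the first failure.
3. Run LSD group comparisons for an outcome only when its group-by-time test is significant at its allotted level, with the pairs tested at that same level, and never on a time effect alone. This controls the three group-by-time tests across outcomes; the pairwise claims are held within each outcome.

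The two-way ANOVA can stay, and neither WOMAC nor OAKHQOL need be demoted.

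**Cost.** Holm costs some power: at its strictest step 79.6% against 90.2% with 54 evaluable, on the f = 0.5 reading. A fixed order costs no alpha but gives up a stand-alone claim on later outcomes if an earlier one fails. Under the Monitoring section, the change must go to the ethics committee as a protocol modification. No extra participants or visits are needed. Recruitment was still open when the article appeared, so the change could be made before analysis.

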**Discussion:**

The present study will compare the effects of two different home-based exercise intervention programs among patients with mild knee OA. The study findings will provide vital information that can be used to design an effective exercise program that aims at delaying the OA progression.

**Trial registration:**

The protocol was registered on 22 December 2020 at ClinicalTrials.gov (registration number: NCT04678609).

## Background

Knee OA commonly affects the elderly and also adults in their 40s [1]. The typical clinical symptoms of knee OA include pain, joint stiffness, muscle weakness, impaired proprioception, and reduced joint motion, all of which can affect patients’ daily activities [2]. With a projection of 250% increase of elderly population aged 65 years and above in Malaysia, Singapore, India, Bangladesh, and the Philippines over the next three decades [3], knee OA will significantly impact the healthcare system [4]. According to the Malaysian Clinical Practice for Osteoarthritis Management, 9.3% of adult Malaysians suffered from knee pain, and more than half of those examined had clinical evidence of OA [5]. Additionally, knee OA patients are predisposed to a higher risk of falls than those without knee OA [6]. Worse still, falls can cast a severe impact on the elderly, leading to severe disability or even death [7]. Hence, the prevention of OA development and progression is vital among the elderly with knee OA.

Exercise intervention recommended by clinical guidelines is a crucial non-pharmacological management for knee OA [8]. Exercise intervention appears to be more effective in the early stage of knee OA before the onset of significant structural damage [9, 10]. Several studies suggested that exercise intervention may improve pain, muscle activity, and strength and functional movement of OA patients [11–15]. Biomechanical factors such as gait velocity and knee adduction moment (KAM) are crucial indicators of OA progression. However, much is not known regarding the effects of exercise on the lower limb biomechanics during gait and sit-to-stand (STS) among mild knee OA patients.

To date, open kinetic chain (OKC) and closed kinetic chain (CKC) exercises have been prescribed for knee OA patients. During OKC exercise, the distal segment of the body parts is not fixed, and it can move freely. Knee extension in the sitting position and straight leg raising (SLR) in the lying position are examples of OKC exercises. On the other hand, during CKC exercise, the distal segment of body parts remains stationary on the ground. Examples of CKC exercises include squat and leg press exercises. Both types of exercises were comparable in terms of their impact on improving pain scale, functional scores, and strength [16]. Moreover, 12 weeks of OKC, CKC, and its combination were found to significantly increase the static and dynamic quadriceps strength and thigh muscle bulk in a study that involved 96 patients with knee OA [17]. However, there is a lack of published studies that evaluate the impact of OKC and CKC on the lower limb biomechanics during gait and STS.

Exercise intervention for OA is usually conducted in the hospital or clinic under the supervision of physiotherapists. However, some patients might face logistics constraints in attending the exercise sessions [18]. To improve the adherence to exercise program, the sessions can be relocated from the hospital to other settings such as at home and in the community [7]. Apart from that, patient education is vital to improve the patients’ understanding of their current condition and to ensure compliance to exercise program and long-term self-management at home [12].

The primary aim of this randomized controlled trial (RCT) is to compare the effects of home-based OKC and CKC exercise intervention programs on pain (visual analog scale), disability scores (Western Ontario and McMaster Universities Arthritis Index), and quality of life scores (Osteoarthritis Knee and Hip Quality of Life) among patients with mild knee OA. Our secondary aim is to compare the effects of OKC and CKC exercises on lower limb biomechanics during walking gait and STS tasks. It is hypothesized that OKC and CKC exercises will result in a significant reduction of pain as well as improved functions and quality of life after 8 weeks of intervention. We also hypothesize a small but clinically relevant change in their biomechanical variables following OKC and CKC intervention. These changes may be significant when compared to the usual care group.

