## Method/design

### Trial design

This study is a randomized controlled trial (RCT) comparing the effects of CKC versus OKC versus the control group in patients with mild knee OA. The effects to be measured include pain, disability, quality of life, and lower limb biomechanics. This protocol will be outlined as per the CONsolidated Standards of Reporting Trials (CONSORT) [19] statement and reported as per Standard Protocol Items: Recommendations for Interventional Trials (SPIRIT) [20]. The flowchart of the study protocol is shown in Fig. 1.

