## Discussion

The prevention of knee OA is different for each individual depending on their risk factors [46]. Targeted individualized prevention techniques to ensure maximum adherence to the exercise program should be planned for each patient [46]. To achieve this, it is crucial to involved knee OA patients in the exercise program to understand their treatment preferences and improve their conditions. Apart from statistically significant differences between patient and control groups, other clinically significant differences can also be important when interpreting the trial results [47, 48]. A decrease of 2 points in the pain score and a decrease of 9.1 scores in the function subscale of the WOMAC questionnaire are examples of clinically relevant improvement [47, 49, 50]. A mere 5% change in KAM was shown to improve OA symptoms [51, 52] which will be considered as a clinically relevant improvement of the KAM in this trial. The results from this trial will provide vital evidence on clinical and biomechanical outcomes following OKC and CKC exercise programs in people with mild knee OA. Additionally, this study will help in the formulation of effective home-based exercise protocols, especially for patients with mild knee OA.

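### The primary-outcome hypothesis names no comparator and does not match the OKC-versus-CKC aim, so it could be declared confirmed from pre-post change alone

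*Protocol article*

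**What the plan says.** The Background states the aim as a comparison of the two programmes: "The primary aim of this randomized controlled trial (RCT) is to compare the effects of home-based OKC and CKC exercise intervention programs", on pain (VAS), disability (WOMAC) and quality of life (OAKHQOL). The hypothesis for the same outcomes follows shortly after: "It is hypothesized that OKC and CKC exercises will result in a significant reduction of pain", together with improved function and quality of life after 8 weeks. It mentions neither the other exercise programme nor the control group.

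The next sentence hypothesises a small biomechanical change. The paragraph then closes with the only comparator wording in the hypotheses: "These changes may be significant when compared to the usual care group". Read most directly, this refers to the biomechanical changes. It is hedged, and it concerns usual care, not OKC against CKC.

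Two other places bear on the point. The Trial design section describes a trial "comparing the effects of CKC versus OKC versus the control group in patients with mild knee OA". The Statistical analysis section plans a two-way ANOVA "to test the within- and across- group comparison" of the VAS, WOMAC and OAKHQOL scores (and the secondary outcomes), with LSD post hoc tests after any significant ANOVA result. It does not say which ANOVA term or pairwise contrast answers the primary question.

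**The concern.** A hypothesis of improvement after 8 weeks is met by a pre-post p-value within an arm. Such a p-value does not separate an exercise effect from whatever else lowers pain over 8 weeks, and the protocol contains several such influences that all arms share:

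- Entry requires a VAS of at least 2 (Recruitment of participants), so regression to the mean is possible.
- Usual care, including pain killers and health education, goes to everyone (Procedure).
- Paracetamol is available to all three groups, to be taken as needed (Interventions).

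A fall in every arm is therefore plausible, though the article does not establish that it will occur.

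At stake is what the trial may claim. If both exercise arms show a significant fall while OKC versus CKC and each arm versus control do not differ, the printed hypothesis would still be satisfied. A statement that the programmes work could then be made without support from any randomised contrast.

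**Working it through.** The plan gives no figure of its own for this point, so there is none to reproduce. The check asks how often the printed hypothesis would be met when exercise does nothing beyond control.

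**Inputs from the article:** 18 evaluable participants per group (Sample size calculation); significance at p < 0.05 (Statistical analysis), taken as two-sided because no side is stated.

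**Assumed inputs, not in the article:** the same mean fall Δ in all three arms, in units of the outcome SD; equal SDs before and after; pre-post correlation ρ; normal data.

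**Within-arm test.** The SD of the change is √(2(1−ρ)). The paired t-test has noncentrality Δ√n / √(2(1−ρ)) on n−1 = 17 degrees of freedom (critical value 2.110). The arms contain different participants, so with a fixed common fall the probability that both exercise arms are significant is the square of the one-arm probability.

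With Δ = 0.5 and n = 18:

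| ρ | SD of change | Noncentrality | One exercise arm significant | Both significant |
|---|---|---|---|---|
| 0.3 | 1.183 | 1.793 | 0.394 | 0.155 |
| 0.5 | 1.000 | 2.121 | 0.516 | 0.267 |
| 0.7 | 0.775 | 2.739 | 0.733 | 0.537 |

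The hypothesis speaks of both programmes, so the last column is the relevant one.

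**Sensitivity to the assumed fall**, at ρ = 0.5:

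| Common fall (SD) | One arm, n = 18 | Both arms, n = 18 | Both arms, n = 22 |
|---|---|---|---|
| 0.3 | 22% | 5% | 7% |
| 0.5 | 52% | 27% | 37% |
| 0.8 | 89% | 80% | 90% |
| 1.0 | 98% | 96% | 99% |

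A simulation of three arms with an identical fall (20,000 runs per scenario) agrees with the table to within rounding. It also shows that:

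- the control arm alone is significant as often as a single exercise arm;
- the OKC-versus-CKC test on change and the group-by-time test each reject in about 5% of trials, whatever the size of the common fall.

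**ANOVA time effect.** With 54 evaluable participants, Δ = 0.5 and ρ = 0.5, the noncentrality is 0.5 × √54 = 3.67 on 51 degrees of freedom, and the time effect is significant in about 95% of trials. A significant two-way ANOVA result is thus easy to obtain from change common to all arms.

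**Precision of OKC versus CKC.** The half-width of the unadjusted 95% CI at 18 per arm is t(0.975; 34) × √(2/18) = 2.032 × 0.333 = 0.68 SD of the variable compared. A non-significant result would leave differences of considerable size open.

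**The case against.** The strongest reply is that the randomised comparison is planned. The Trial design section names three arms to be compared on pain, disability and quality of life. The ANOVA covers across-group as well as within-group comparison of these outcomes. The hypothesis paragraph mentions usual care, and the Discussion refers to differences between patient and control groups. A reader might infer from the hypothesis alone that the trial's conclusion will not rest on the randomised comparison. The documents do not support that: nothing says the within-group part will decide. What they support is that the conclusion could be drawn from it. It is also fair that naming the decisive ANOVA term is often left to a fuller document. That does not cover the hypothesis sentence, which is printed and does not match the printed aim.

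Three further readings are tempting and should be resisted.

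- The Background says "Both types of exercises were comparable in terms of their impact on improving pain scale, functional scores, and strength". A reader might take this as an expectation that the arms will not differ here. It is a past-tense report of a cited study, and the article states no expectation for OKC versus CKC.
- The article nowhere says it will report both programmes as effective and comparable. That is one possible misreading of a null result, not a plan.
- The Discussion gives "A decrease of 2 points in the pain score" as an example of clinically relevant improvement. It might look like a ready equivalence margin, but it is offered as an improvement in a patient's score, not as a between-arm margin.

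Finally, the percentages depend on assumed inputs, and the range from 5% to 96% is wide. That objection stands for the size. It does not touch the direction: with any common fall, the within-arm tests reject more often than their nominal level, while the between-arm tests do not.

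**Conclusion.** The point holds in limited form. The primary-outcome hypothesis has no comparator, it does not match the primary aim, and the analysis section gives within- and across-group comparison equal standing. As written, the hypothesis can be declared confirmed while every randomised contrast is null.

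For a common fall of 0.5 SD at 18 per arm and ρ of 0.3, 0.5 and 0.7, one exercise arm is significant in about 39%, 52% and 73% of trials, and both in about 15.5%, 27% and 54%, against 5% for a between-arm test. These figures illustrate the mechanism and do not predict this trial's result. The change is worth making because it ties the conclusion to the randomisation at almost no cost.

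**What to change.** Restate the primary hypotheses as between-arm differences in change to week 8: OKC versus CKC, which is the stated aim, and each programme versus control. Say that they are judged by the group-by-time term or by a baseline-adjusted between-arm contrast. Report within-arm change descriptively, and not as evidence of efficacy. Report OKC versus CKC with its 95% CI, and state that a non-significant result will not be read as comparability. Do not use the 2-point improvement as an equivalence margin.

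The change is to the wording of the hypotheses and to how the planned tests are used. It needs no new data or visits. The article reports recruitment as ongoing, so on that timeline it can be made before analysis. The cost is that the easily significant pre-post p-values are given up. Naming three contrasts also makes their multiplicity visible, so the plan should say which contrast is primary or how the three are handled together.
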